## Abstract

**Background:**

Rotator cuff tears are a common shoulder injury, but they sometimes remain undiagnosed, as symptoms can be limited. Altered shoulder biomechanics can lead to secondary damage and degeneration. In biomechanical analyses, the shoulder (ie, the glenohumeral joint) is normally idealized as a ball-and-socket joint, even though a translation is often observed clinically. To date, no conclusive changes in glenohumeral translation have been reported in patients with rotator cuff tears, and it is unknown how an additional handheld weight that is comparable to those used during daily activities will affect glenohumeral translations in patients with rotator cuff tears.

**Objective:**

This study aims to assess the load-induced glenohumeral translation (liTr) in patients with rotator cuff tears and its association with the load-induced changes in muscle activation (liMA).

**Methods:**

Patients and asymptomatic controls will be recruited. Participants will fill out health questionnaires and perform 30° arm abduction and adduction trials, during which they will hold different handheld weights of a maximum of 4 kg while motion capture and electromyographic data are collected. In addition, fluoroscopic images of the shoulders will be taken for the same movements. Isometric shoulder muscle strength for abduction and rotation will be assessed with a dynamometer. Finally, shoulder magnetic resonance images will be acquired to assess muscle status and injury presence. The dose-response relationship between additional weight, liTr, and liMA will be evaluated.

**Results:**

Recruitment and data collection began in May 2021, and they will last until the recruitment target is achieved. Data collection is expected to be completed by the end of 2022. As of November 2022, data processing and analysis are in progress, and the first results are expected to be submitted for publication in 2023.

**Conclusions:**

This study will aid our understanding of biological variations in liTr, the influence of disease pathology on liTr, the potential compensation of rotator cuff tears by muscle activation and size, and the association between liTr and patient outcomes. The outcomes will be relevant for diagnosis, treatment, and rehabilitation planning in patients with rotator cuff tears.

**Trial Registration:**

ClinicalTrials.gov NCT04819724; https://clinicaltrials.gov/ct2/show/NCT04819724

**International Registered Report Identifier (IRRID):**

DERR1-10.2196/43769

## Introduction

The shoulder (ie, glenohumeral joint) is a unique joint primarily stabilized by the rotator cuff muscles [1]. These muscles facilitate shoulder motion and center the glenohumeral joint [2]. This type of stabilization facilitates a large range of motion [2], which is a prerequisite for many daily, occupational, and recreational activities. An injury to the rotator cuff can therefore lead to an unstable joint and affect joint functionality, negatively affecting patients’ activities and quality of life. Furthermore, altered shoulder biomechanics can lead to secondary damage and degeneration, such as tendinopathy or osteoarthritis [3]. The motion of a healthy shoulder mainly comprises rotation and very small to no translation due to stabilization through muscle forces. Glenohumeral stability is affected by the muscle cross-sectional area; the level of muscle activation; and the shoulder anatomy, including the critical shoulder angle and glenoid inclination [4-6].

Degenerative partial and complete ruptures of the rotator cuff are common injuries with a steady increase in prevalence with aging [7]. Yamamoto et al [8] reported a total prevalence of rotator cuff tears of 20.7%, with the 0% prevalence in the age group of 20 to 29 years increasing to 50% in those aged 80 to 89 years. The clinical manifestation of degenerative rotator cuff tears varies largely among patients; some have no complaints, and the diagnosis is an incidental finding, while others have severe pain and a limited range of motion that is marginally restored with conservative treatment [9]. In patients with end-stage degenerative rotator cuff lesions, especially with tears of the supraspinatus muscle, this deficit manifests radiologically as a narrowing of the subacromial space [10], presumably caused by the muscular force of the deltoid muscle pulling the humeral head superiorly toward the acromion.

The general population study of Yamamoto et al [8] revealed that 36% of patients with current symptoms had rotator cuff tears, while 17% of asymptomatic participants were also diagnosed with rotator cuff tears. However, to date, possible reasons for this symptomatic discrepancy are poorly understood. Differences in symptomatic and functional limitations may be related to glenohumeral instability in patients with rotator cuff tears. A dysfunctional rotator cuff potentially leads to insufficient joint centering, and tears of the supraspinatus tendon may cause a superior glenohumeral translation. A greater superior translation may affect the pressure around the glenoid cavity and the labrum, possibly leading to pain and impingement and thereby limiting shoulder mobility.

Common kinematic models assume that the glenohumeral joint is a ball-and-socket joint [11], without any consideration of the common clinically observed translation. No conclusive changes in shoulder translation have yet been reported in patients with rotator cuff tears [12-15]. Moreover, it is still unknown how additional handheld weight (comparable to that experienced in situations during daily, occupational, or recreational activities) affects glenohumeral translation in patients with rotator cuff tears. Intact shoulder muscles’ compensation mechanisms for the lacking muscle force of injured muscles are also largely unknown. Such mechanisms may lead to overloading of the uninjured muscles, which can eventually lead to degenerative changes secondary to the original injury.

The current state of research in the field and in our research shows that our proposed framework, applied in a previous pilot study [16] for assessing load-induced glenohumeral translation (liTr), is feasible. Our preliminary clinical analyses have shown that many people aged 45 years and up have degenerative tendon changes despite an absence of symptoms. Clinical observations and results reported in the literature raise the following questions: (1) Is the load-induced increase in deltoid muscle activity with increasing additional load in patients with symptomatic rotator cuff tear greater than that in asymptomatic or healthy joints? (2) Does liTr in the injured joint increase with increasing additional load? (3) Is liTr greater in patients with rotator cuff tears than in age-matched asymptomatic controls and young healthy controls? (4) Is liTr associated with load-induced changes in muscle activation (liMA)? (5) Is there a correlation between the patient’s functional scores and liTr? (6) Is liTr related to muscle morphology, tear size and type, and shoulder anatomy? (7) Are measurements of liTr using motion analysis and single-plane fluoroscopy comparable?

Evidently, there are a variety of factors to consider, including anatomical, morphological, functional, and injury-related factors. Answering these questions will provide information to help clarify the biomechanical limitations of an injured rotator cuff and their impact on treatment, therapy, and daily life. Hence, this study aims to assess the dose-response relationship between liTr and liMA in patients with rotator cuff tears and in age-matched asymptomatic and young healthy participants.

## Methods

### Objectives and Hypotheses

This study will test the overall hypothesis that rotator cuff tears affect glenohumeral translation and that this functional instability depends on the additional load applied, anatomical and morphological variations, and the type and severity of the injury. We propose that greater liMA of the deltoid muscle is associated with greater liTr and that liTr is altered by rotator cuff injury and may be related to patients’ functional scores, muscle cross-sectional area, tear size and type, critical shoulder angle, and glenoid inclination. We also propose that this person-specific relationship is associated with corresponding load-dependent changes in shoulder muscle activity.

Our primary objective is to investigate the dose-response relationship between liMA and liTr in patients with rotator cuff tears and asymptomatic control participants.

Hypothesis 1 is as follows: liMA is positively associated with liTr. Because the shoulder is primarily stabilized by rotator cuff muscles, we expect that the presence of a muscle tear will require additional activity of the remaining intact muscles to stabilize the shoulder. Hence, the dose-response relationship between additional load and relative change in muscle activity with rotator cuff tears will be stronger than in uninjured shoulders.

The secondary objectives are to investigate the in vivo dose-response relationship between additional weight and glenohumeral translation, to understand the biological variation in liTr, the influence of disease pathology on the liTr, the potential compensation by muscle activation and size, and the influence of liTr on patient outcomes. The secondary hypotheses are listed as follows:

Hypothesis 2.1: liTr is greater in shoulders with rotator cuff tears than in healthy shoulders.Hypothesis 2.2: An increase in liTr is part of natural aging, and its variation is related to sex and shoulder anatomy assessed by the critical shoulder angle and the glenoid inclination.Hypothesis 2.3: liTr increases with injury severity and depends on injury type.Hypothesis 2.4: liMA and side-to-side differences in muscle size (ie, muscle cross-sectional area) increase with the presence of injury and injury severity.Hypothesis 2.5: There is a biological variation in liMA and in the compensation effect by muscle activation and muscle size (ie, muscle cross-sectional area).Hypothesis 2.6: Large values of liTr are associated with poor functional scores.

In this study, the correlation between liMA and liTr and their relation to patients’ functional scores, muscle activation and size, tear size and type, and shoulder anatomy (critical shoulder angle and glenoid inclination) will be analyzed.

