### Study Design and Participants

This study entails cross-sectional, experimental multimodal (clinical, biomechanical, radiological) data collection with multiple conditions and a control group. A total of 25 patients aged 45 to 85 years with unilateral symptomatic rotator cuff tears will be recruited from our clinic. Orthopedic surgeons will inform patients who fulfill the inclusion criteria about the study, and eligible candidates will be contacted. Additionally, 25 asymptomatic controls will be recruited to achieve the same age and sex distribution as in the patient group. Moreover, because of the clinically observed high prevalence of rotator cuff tears in persons without symptoms, we will also recruit 25 sex-matched young asymptomatic controls aged between 20 and 30 years to allow for elucidating the effect of the natural aging process. Detailed inclusion and exclusion criteria for the cohorts are shown in Textbox 1.

Inclusion and exclusion criteria for this study.

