#### MRI Visualization

MRI will be performed using a 3T scanner (Prisma, Siemens Healthineers) with dedicated shoulder and body array coils. No contrast agent will be administered to the participants. Both shoulders will be scanned. The MRI protocol consists of an axial proton density turbo spin echo (TSE) sequence with fat saturation, a sagittal T1-weighted TSE sequence, a sagittal and a coronal T2-weighted BLADE sequence, and a coronal T1-weighted volumetric interpolated breath-hold examination Dixon sequence (Table 2).

**Table 2 table2:** Characteristics of the MRI^a^ sequences.

MRI sequence	Repetition time/echo time (ms)	Slice thickness (mm)	Field of view (mm)	Matrix
PD^b^ TSE^c^ FS^d^ axial	4500/34	2	140	320 × 320
T1 TSE sagittal	762/11	3	159	384 × 384
T2 BLADE sagittal	4210/72	3.6	160	320 × 320
T2 BLADE coronal	3400/75	3.6	150	320 × 320
T1 VIBE^e^ Dixon coronal	4.04/1.23 (TE^f^1) and 2.46 (TE2)	1.3	238 × 332	184 × 256

^a^MRI: magnetic resonance imaging.

^b^PD: proton density.

^c^TSE: turbo spin echo.

^d^FS: fat saturation.

^e^VIBE: volumetric interpolated breath-hold examination.

^f^TE: echo time.

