#### Muscle Cross-sectional Area

Measurements of the muscle cross-sectional area will be performed on the MRI images using dedicated software (Sectra PACS, Sectra Medical Systems). The cross-sectional area of all rotator cuff muscles will be measured at 2 different positions on parasagittal reformatted images [4]. The cross-sectional area of the deltoid will also be measured on the axial plane at the middle of the glenoid [4].

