### Statistics and Determination of Sample Size

All study-related data will be entered into and stored using a web-based Research Electronic Data Capture (REDCap; Vanderbilt University) system [50,51]. All statistical analyses will be performed in R statistical software [52]. Overall, 25 patients with 1 symptomatic shoulder with a rotator cuff tear, 25 age- and sex-matched asymptomatic control participants, and 25 sex-matched young control participants will participate in this study. This means that a total of 150 shoulders will enter the analysis. Comparisons between the fluoroscopy-based liTr and motion capture–based liTr will be made. Reproducibility and agreement will be assessed by the mean and standard deviation of differences and Bland-Altman plots. Precision in estimating the liTr will be assessed by average relative standard errors and *R*^2^ values from a global model. Potential deviations from a linear relationship will be assessed by random effects models for a quadratic term. The influence of covariates on the liTr and the biological variation of liTr will be assessed by mixed models applied to the original glenohumeral translation measurements with the liTr as a random effect. Dependence between the shoulders will be considered by bivariate random effects.

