#### Sample Size Calculation

From a pilot study data consisting of 18 participants (8 patients and 10 asymptomatic controls), we found a correlation of 0.37 between the liTr and liMa for the treatment group and an overall correlation of 0.63 for all individuals included in the study [16]. Using these findings, we considered different correlation scenarios between liTr and liMa for a different power of analysis (Figure 3). For a 5% significance level, 90% power, and a correlation of 0.37, we need 76 shoulders. Considering a possible dropout rate of 5%, we need 80 shoulders for the first hypothesis in this study. We also powered the analysis for the secondary hypotheses and used the repeatability investigation, which suggested a measurement error with a standard deviation of 0.16 mm for the sphere method when assessing the liTr by comparing a load of 3 kg with no load. Moreover, the pilot study revealed a population standard deviation of 1.09 mm for the liTr, suggesting a substantial biological variation in the liTr. Thus, it should be possible to estimate this variation and assess the effect of covariates. Based on our clinical findings, we expect to observe incidental findings of rotator cuff tears in two-thirds of asymptomatic shoulders in participants aged 45 years or older. Therefore, we expect to have 75 shoulders with rotator cuff tears. Within the 75 shoulders with rotator cuff tears, it will be possible to detect a difference of 0.8 mm in liTr with a power of 90%.

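### Hypothesis 2.4 measures muscle size as a side-to-side difference, although the plan's own count has about two-thirds of patients' other shoulders torn; this can dilute the injury effect by up to two-thirds

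*Protocol article*

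**What the plan says.** Under Objectives and Hypotheses, Hypothesis 2.4 reads: "liMA and side-to-side differences in muscle size (ie, muscle cross-sectional area) increase with the presence of injury and injury severity". The muscle-size outcome is thus a within-person difference; liMA in the same sentence is not worded that way.

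Under Muscle Cross-sectional Area, "The cross-sectional area of all rotator cuff muscles will be measured at 2 different positions on parasagittal reformatted images", and the deltoid is measured as well. Neither place gives a reference side or a sign for the difference. Muscle area is listed among the Other end points.

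Under Sample Size Calculation the plan states that "we expect to observe incidental findings of rotator cuff tears in two-thirds of asymptomatic shoulders in participants aged 45 years or older". It goes on: "Therefore, we expect to have 75 shoulders with rotator cuff tears". The Statistics section gives the groups as "25 patients with 1 symptomatic shoulder with a rotator cuff tear, 25 age- and sex-matched asymptomatic control participants, and 25 sex-matched young control participants", and adds: "This means that a total of 150 shoulders will enter the analysis".

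Under Study Design and Participants, "A total of 25 patients aged 45 to 85 years with unilateral symptomatic rotator cuff tears will be recruited from our clinic". The eligibility textbox likewise speaks of a diagnosed unilateral tear. Its item on the opposite joint concerns history and symptoms, not tendon status on MRI. The MRI section says: "Both shoulders will be scanned".

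**The concern.** Tear status and severity belong to a shoulder; the muscle-size outcome in Hypothesis 2.4 belongs to a pair of shoulders. The two match only when the opposite shoulder is intact. By the plan's own expectation it is usually not, in patients or in older controls.

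When a person goes from one torn shoulder to two, injury presence goes up while the expected side-to-side difference goes down. The hypothesised increase is therefore not monotone in the exposure it is tested against. At stake is the secondary objective on compensation through muscle size: a real effect of tears on muscle area could be diluted, and bilateral disease could be read as no change in muscle size.

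**Working it through.** **1. Reproduce the plan's count.** Inputs: 25 symptomatic shoulders, 25 contralateral patient shoulders and 50 older-control shoulders (group sizes from the Statistics section), and the two-thirds expectation from Sample Size Calculation.

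- With contralateral shoulders: 25 + 2/3 × (25 + 50) = 25 + 50 = 75, exactly the stated total.
- Without them: 25 + 2/3 × 50 = 58.3.

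So the two-thirds expectation is applied to patients' other shoulders. It implies 25 × 2/3 = 16.7 patients torn on both sides and 8.3 torn on one side only.

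**2. Direction of the outcome.** Let a symptomatic tear shift muscle area by D and a silent contralateral tear by kD, with k assumed. The expected side difference is 0 with no tear, D with one symptomatic tear and D(1 − k) with both sides torn. For any k above 0 it falls between one tear and two.

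**3. Mean side difference in patients.** With two-thirds of contralateral shoulders torn, it is D × (1 − 2k/3). With the spread of the difference held fixed, the required number rises by 1/(1 − 2k/3)².

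| k (assumed) | Effect kept | Required n |
|---|---|---|
| 1 | 0.33D | 9-fold |
| 0.75 | 0.50D | 4-fold |
| 0.5 | 0.67D | 2.25-fold |

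**4. Illustration of power.** One-sample t test of the mean signed difference in 25 patients, two-sided 5%, k = 1. The documents give no standard deviation (SD) for muscle area, so these inputs are assumed: a tear effect d of 0.5 to 1.0 SD and a between-side correlation ρ of 0.5 to 0.8. The variance of the difference is 2(1 − ρ), plus d² × 2/9 for the mix of torn and intact contralateral sides.

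- Other side intact in all patients: power 67% (d = 0.5, ρ = 0.5) to 100% (d = 1.0, ρ = 0.8).
- Other side torn in two-thirds: power 12% to 53% at the same two corners.

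**5. Absolute differences do not repair it.** By simulation with k = 1 and tears independent between a control's two sides, the mean absolute side difference in older controls and in patients is 0.84 against 0.83 SD (d = 0.5, ρ = 0.5) and 0.74 against 0.68 SD (d = 1.0, ρ = 0.8). Injury presence would not separate these two groups.

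**6. Informative participants.** Those torn on one side only would number about 8.3 patients and, with independent sides, 25 × 2 × 2/3 × 1/3 = 11.1 older controls.

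**The case against.** The strongest reply is that the article fixes no estimator for muscle area. Hypothesis 2.4 is one sentence, and how a secondary hypothesis becomes a model is commonly left to the full protocol or analysis plan. Both shoulders are scanned and tears are graded, so the side difference could be regressed on the side difference in tear status or severity. Under an additive tear effect that contrast is unbiased: pairs with equal tears add little information but no bias. This stands, and it means the dilution is conditional. It arises if the difference is related to group or to person-level injury presence. However, the article does not state the rescuing analysis, and one that follows the hypothesis as worded relates a paired difference to injury presence.

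It also stands that 0.33D needs silent tears to act as strongly as symptomatic ones, which the documents do not say. Hypothesis 2.4 itself expects the effect to grow with severity, so a severity contrast can survive where the two sides differ. A side difference has a real merit too: it removes between-person variation in muscle size.

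A reader might infer more, namely that the injury effect cancels altogether or changes sign. The documents do not support that. Cancellation is complete only in people whose two sides are equally affected. The mean difference in patients turns negative only if 2k/3 exceeds 1, that is k above 1.5. An opposite direction is to be expected only when bilateral is compared with unilateral disease. Nor can the 17% in the Introduction serve as a milder prevalence here: it is a share of asymptomatic participants in a general population study, not of shoulders from age 45.

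**Conclusion.** The point holds as a minor one. By the plan's own count, about 17 of 25 patients lack an intact reference shoulder, so the side-to-side difference is a poor outcome for injury presence. If it is related to group or to person-level presence, the effect in patients is attenuated by up to two-thirds for k between 0 and 1. This rests on the plan's two-thirds expectation and on the assumed k; the power figures rest further on assumed effect sizes and correlations. Only the muscle-area half of one secondary hypothesis is affected. The primary hypothesis and the liMA half of Hypothesis 2.4 are not.

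Separately, the description of patients as having a unilateral tear and the two-thirds expectation need reconciling. If unilateral refers to symptoms, the count of 75 stands and the reference-side problem follows. If it means the other shoulder is intact, the problem disappears in patients, but the count becomes 58.3 and the detectable difference of 0.8 mm in liTr, which is based on 75, loses its basis.

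**What to change.** - Restate the muscle-size part of Hypothesis 2.4 at shoulder level. Model cross-sectional area on each shoulder's MRI tear status and severity, adjusted for sex, age, body size and side, with participant as random effect.
- Equivalently for the within-person part, regress the side difference on the side-to-side difference in MRI tear status or severity.
- Keep the raw side difference as a descriptive figure for participants whose contralateral shoulder is intact on MRI, with its reference side and sign stated.
- Say whether unilateral refers to symptoms or to tendon status, and make the expected number of torn shoulders agree with it.

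The cost is wording. Both shoulders are already scanned, tears are already classified, and random effects for paired shoulders are already planned for liTr. There is a small downside: the random-effect model also uses between-person information and so depends on adequate covariate adjustment. Reporting the within-person estimate alongside it covers this, though that estimate draws mainly on the participants whose two shoulders differ in tear status or severity.
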